### Secondary endpoints

The secondary endpoints are operation time, hospital stay, complications (e.g. infection), cost-efficiency analyses, time to return to daily activities/work and recurrence after Lichtenstein or TIPP procedures.

### Design

TULIP is a double-blind, randomised controlled trial. Randomisation will be performed by pulling a sealed double blind envelope in the trial centre after contact by telephone prior to incision. Obviously, the surgeons know which technique they are performing during operation. The investigator assessing the outcome on the outpatient department is not informed. Operation reports are blinded and no (digital) access is permitted or possible for the person assessing outcomes. The patient does not know which procedure has been performed because it is written down on paper and not mentioned in theatre.

### Patients

A total of 300 patients, with a unilateral primary groin hernia, visiting the outpatient clinics at the St. Elisabeth Hospital or TweeSteden Hospital in Tilburg will be randomised (figure 1).

Analyses of inguinal hernia patients in the past showed a number of approximately 600-700 per year in both hospitals, equally divided. This number is the sum of both hospitals and includes recurrences, children/elderly, incarcerated and bilateral inguinal hernia's. Apart from a positive informed consent, a lower amount can/will be included. Data will be collected by VAS-diary and SF36-list (Health Status/Quality of Life). Forms will be filled in by the patients at 14 days, 3 months and one year after surgery during follow up (figure 1).

**Figure 1 F1:**
[figure not shown]

### Inclusion criteria

• Primary unilateral groin hernia

• Age > 18, < 80 years

• ASA classification 1-3

• Signed informed consent letter

### Exclusion criteria

• Recurrent hernia

• Age <18 or >80 years

• Scrotal hernia(s)

• ASA classification >4

• Acute incarcerated inguinal hernia(s)

• Psychiatric disease or other reason making follow up or questionnaires unreliable

• Previous preperitoneal surgery (e.g. radical prostatectomy)

### Ethics, informed consent

This study is conducted in accordance with the principles of the Declaration of Helsinki and "Good Clinical Practice Guidelines". The independent ethics committee of both participating hospitals approved the final protocol. Oral and written informed consent in form is obtained from the patient before inclusion in the trial.

The TULIP Trial is registered at: .

### Surgical Techniques

All patients will be operated via anterior approach with a skin incision two centimetres above the Poupart ligament. In half of the study population the groin hernia will be corrected according to Lichtenstein, as described by Amid et al. [27]. This is the reference treatment advised by the Dutch Society of Surgeons [28]. The Lichtenstein technique will be attempted to present-day insights; a soft mesh will be used instead of the polypropylene mesh [29].

The other 150 inguinal hernia patients will be operated by the transinguinal preperitoneal (TIPP) technique with Polysoft^® ^mesh as described by Pélissier et al. [26]. In this technique an inguinal incision 8-10 cm long is made, the external oblique aponeurosis is divided and the cord lifted on a tape. The cremaster muscle is divided around the internal orifice, but not striped, and the sac is dissected. The technique of placement of the Polysoft^® ^mesh into the preperitoneal space adapts anatomically to the type of hernia. Type of hernia will be assessed using the European Hernia Society groin hernia classification [30]. This classification is simple and easy to remember. The size of the hernia orifice is registered as 1 (≤ 1 finger), 2 (1-2 fingers) or 3 (≥ 3 fingers) accompanied with L (lateral), M (medial) or F (femoral). All the hernia's will be primary (P) classified according to the inclusion criteria so recurrent (R) will not be assessed in our population. Example; a lateral inguinal hernia with an orifice of 2 fingers and a primary origin will result into L2P.

In indirect hernias high dissection of the sac is performed and the sac is thus reduced in the pre peritoneal space (PPS) through the internal ring. Blunt dissection is carried out in the PPS, through the internal orifice and is then extended deep to epigastric vessels and transverse fascia, in the direction of the pubic spine, beyond its level. The patch is introduced in the PPS via the internal orifice. In regional or local anaesthesia asking the patient to strain allows correct anatomical spreading of the mesh, which is applied to the deep aspect of the fascia. The assessment is done by asking the patient to strain and to cough. External oblique aponeurosis was repaired superficial to the cord to restore the normal anatomy.

In direct hernias, after division of the cremaster so as to check the internal orifice for an indirect sac, the transverse fascia is divided circularly around the hernia bulge and the sac is reduced. Blunt dissection is carried out in the PPS, medially in the direction of the pubic spine and laterally behind the epigastric vessels in direction of the iliac spine. The patch is introduced through the transverse fascia opening and spread in the PPS so as to cover all the weak inguinal area. When an indirect sac, even if it is small, is associated to the direct one, both sacs are dissected and reduced.

### Escape medication

A standardized general anesthesia/spinal anesthesia protocol will be used in both groups in combination with a standardized post operation regimen, based on VAS scores for pain and nausea. These regimes are based on current and acceptable practice and the standardization serves to avoid unnecessary bias.

The choice of anesthesia technique will be left, in principle, to the preference of the patient. All patients will be seen, pre-operatively at the pre-operative screening outpatient clinic at one of the two locations. Standardized pre- and postoperative medication will be handed out to the patients to be used each day, during the first 5 days postoperatively, including any part of this period that the patient may already have been discharged. This includes, but is not limited to, paracetamol 1 gram four times daily and diclofenac 50 mg 3 times daily and as rescue medication zaldiar 50 mg 3 times daily when regular painkillers are not satisfying.

### Statistical analysis

The analysis will be performed on the basis of intention-to-treat principles.

It is anticipated that the use of TIPP technique with soft mesh at least will lead to a reduction in postoperative chronic pain from 25% to 10%. The sample size calculation is based on α = 0,05 and a power of 80%. This leads to a required sample size of 300 patients. Taking into account a 5% loss-to-follow up, a total of 2 × 158 patients will be randomized. There are three postoperative follow up visits at the outpatient department at two weeks, three months and one year for both groups (Lichtenstein and TIPP). The expected study end is December of 2010 (after 1,5 years inclusion period).

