**Methods:**

The TULIP is a double-blind randomised controlled trial in which 300 patients will be randomly allocated to anterior inguinal hernia repair according to Lichtenstein or the transinguinal preperitoneal technique with soft mesh. All unilateral primary inguinal hernia patients eligible for operation who meet inclusion criteria will be invited to participate in this trial. The primary endpoint will be direct postoperative- and chronic pain. Secondary endpoints are operation time, postoperative complications, hospital stay, costs, return to daily activities (e.g. work) and recurrence. Both groups will be evaluated.

Success rate of hernia repair and complications will be measured as safeguard for quality.

To demonstrate that inguinal hernia repair according to the transinguinal preperitoneal (TIPP) technique reduces postoperative pain to <10%, with α = 0,05 and power 80%, a total sample size of 300 patients was calculated.

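### The stated inputs (chronic pain 25% vs 10%, α 0.05, power 80%) give 194 to 226 patients, not 300, so at least one of them does not belong to this sample size

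*Protocol article*

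**What the plan says.** The Statistical analysis section of the protocol article gives a complete sample size statement. The effect is a "reduction in postoperative chronic pain from 25% to 10" per cent with the TIPP technique. On error rates it says: "The sample size calculation is based on α = 0,05 and a power of 80" per cent. The result follows directly: "This leads to a required sample size of 300 patients". Only then is attrition brought in: "Taking into account a 5% loss-to-follow up", "a total of 2 × 158 patients will be randomized".

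The Methods paragraph of the abstract repeats the calculation: "with α = 0,05 and power 80%, a total sample size of 300 patients was calculated".

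Neither place says whether the test is one- or two-sided, which test or formula was used, or whether α was adjusted.

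**The concern.** A fall from 25% to 10% is a large difference, and 150 evaluable patients per arm looks too many for 80% power to detect it. The plan states both the inputs and the result, so the calculation can be repeated and either agrees or does not.

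Chronic pain is the only outcome used to size the trial, and this statement is the only justification given for its size. If the figures do not belong together, an ethics committee cannot tell from the text why 300 patients are needed. A reader of a null result would also take the chance of missing a fall to 10% to be 20%, when for this sample size it is well below that. If the effect behind the 300 was smaller than the one printed, the plan misreports its own target difference.

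**Working it through.** **Inputs**
- p₁ = 0.25 (Lichtenstein), p₂ = 0.10 (TIPP), difference d = 0.15: Statistical analysis.
- α = 0.05, power 80%: Statistical analysis and abstract.
- Equal arms: from the 2 × 158 in Statistical analysis.
- Sidedness is not stated. Two-sided is assumed (z = 1.960 and 0.842); one-sided is tried below.

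**The attrition step reproduces.** 300 / 0.95 = 315.8, rounded up to 316 = 2 × 158. So 300 is the evaluable number before any allowance for loss.

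**The 300 does not reproduce.** Per arm:

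1. Unpooled variance: n = (1.960 + 0.842)² × (0.25 × 0.75 + 0.10 × 0.90) / 0.15² = 96.8, so 97 per arm, **194 in total**.
2. Pooled variance under the null, with mean proportion p̄ = (0.25 + 0.10)/2 = 0.175: n = [1.960 × √(2 × 0.175 × 0.825) + 0.842 × √(0.1875 + 0.09)]² / 0.15² = 99.5, so 100 per arm, **200 in total**.
3. Continuity correction of the pooled figure: n′ = (n/4) × [1 + √(1 + 4/(n × d))]² with n = 99.5 and d = 0.15 gives 112.5, so 113 per arm, **226 in total**.

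For Fisher's exact test, about 110 per arm (220 in total) reaches 80% power. The largest of these totals, 226, is 74 below 300; the smallest, 194, is 106 below.

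**Could something left unsaid close the gap?**

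| Change to the stated inputs | Total |
|---|---|
| One-sided α 0.05 (unpooled / pooled / corrected) | 154 / 158 / 184 |
| α halved to 0.025, two-sided | 236 / 242 / 268 |
| α = 0.05/3, continuity-corrected | 294 |
| α = 0.01, pooled | 298 |
| Power 90% (unpooled / pooled / corrected) | 260 / 266 / 292 |
| 25% vs 12.5%, power 80% (unpooled / pooled / corrected) | 300 / 304 / 336 |
| 25% vs 12%, power 80% (pooled / corrected) | 278 / 308 |

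One-sided testing moves further from 300. Each row that comes close to 300 replaces an input that the document prints: α, power or the TIPP rate.

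**Power at the stated size.** Exact binomial power, two-sided α 0.05:

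| Per arm | Rates | Chi-square | Fisher |
|---|---|---|---|
| 150 | 25% vs 10% | 93.8% | 91.6% |
| 150 | 25% vs 12.5% | 80.2% | 75.6% |
| 150 | 25% vs 12% | 83.7% | 79.5% |
| 142 | 25% vs 10% | 92.6% | 90.0% |

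The last row covers the abstract and the Patients section, which speak of 300 patients randomised rather than 316: 150 × 0.95 = 142.5, or about 142 evaluable per arm.

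**The case against.** The strongest reply is that the error does no harm to the trial's inference. At the stated effect and α the trial has more power than it claims, and nothing about recruitment need change. That stands, and it limits the severity.

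A second reply is that a journal article condenses a fuller protocol, which might contain an α adjustment. Direct postoperative pain and chronic pain are both named in the primary endpoint, so an adjustment is conceivable. This stands in part. It means that the fault cannot be pinned on power or effect alone, since a stricter α is a third route to about 300. It does not rescue the printed statement: the article gives α = 0.05, and halving α for two outcomes still gives at most 268.

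Two stronger readings are tempting. A reader might infer that the sponsor really planned for 25% vs 12.5%, because that comes so close to 150 per arm. The document does not support this: no such rate appears, the Statistical analysis section presents the fall to 10% as a minimum, and the abstract speaks of less than 10%. The match also depends on the formula chosen, as the corrected version gives 336. The near match at 90% power likewise needs the continuity correction. A reader might also infer that a faulty calculation leaves the trial too small. The power figures show the opposite for the stated effect.

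**Conclusion.** The sample size statement is wrong as printed: its inputs give 194 to 226 evaluable patients, and 300 is 33% (74/226) to 55% (106/194) more than they require. At least one of power, effect and α does not belong to the 300, and the document does not show which. With 150 evaluable per arm, the chance of missing a true fall from 25% to 10% is about 6% (chi-square) or 8% (Fisher), not 20%.

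This rests on a two-sided test, equal arms and a simple comparison of two proportions. A one-sided test widens the gap. If only 300 are randomised and 5% are lost, power is still 90% or more after rounding.

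Severity is moderate: the calculation cannot be reproduced and misstates the trial's power, but it errs on the safe side and leaves the design valid.

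**What to change.** Keep the recruitment target. In the Statistical analysis section and the Methods paragraph of the abstract, name the sidedness and the test or formula, and replace the power statement with one that fits the size. For example:

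> With 150 evaluable patients per arm, the trial has about 94% power (two-sided chi-square test, α 0.05; 92% with Fisher's exact test) to detect chronic pain of 25% vs 10%. About 80% power corresponds to 25% vs 12.5% by the chi-square test, or 25% vs 12% by Fisher's exact test.

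The test must be named beside each figure, because the detectable effect differs between the two tests. If a different effect or a stricter α was in fact used to reach 300, state that input and its reason instead.

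The cost is wording in two places. Recruitment, randomisation and follow-up are unaffected.

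### The number to randomise is 300 in some sections and 2 × 158 = 316 in Statistical analysis; stopping at 300 with the expected 5% loss leaves 285 evaluable, below the stated requirement of 300

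*Protocol article*

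**What the plan says.** The Statistical analysis section works in two steps. From an anticipated fall in chronic pain from 25% to 10%, with α = 0.05 and 80% power, it arrives at a base figure: "This leads to a required sample size of 300 patients". It then inflates that base: "Taking into account a 5% loss-to-follow up", it says, "a total of 2 × 158 patients will be randomized". The number required is therefore 300 and the number to randomise is 316.

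Other sections give a different number to randomise:

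- Abstract, Methods: "300 patients will be randomly allocated to anterior inguinal hernia repair".
- Patients: "A total of 300 patients, with a unilateral primary groin hernia", which that sentence goes on to say will be randomised.
- Surgical Techniques: half of the study population has the Lichtenstein repair, and "The other 150 inguinal hernia patients will be operated by the transinguinal preperitoneal (TIPP) technique". This states no total, but 150 as one half implies 300.

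**The concern.** The Abstract, the Patients section and Statistical analysis all describe the same quantity, the number of patients allocated at random. The difference therefore cannot be explained by reading 300 as evaluable patients and 316 as randomised patients. In the Abstract and Patients section the figure of 300 is attached to randomisation itself, so the allowance for loss to follow-up is missing there.

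The number to randomise is an operating figure. It bears on how long the randomisation list and the series of sealed envelopes must be, and on when recruitment closes. If the trial closes at 300, it meets the Patients section but falls short of Statistical analysis by 16 randomised patients. If it closes at 316, it meets Statistical analysis and exceeds the total in the Abstract and the Patients section. Either way, the final report could be read as under- or over-recruited against its own protocol.

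**Working it through.** **Inputs** (all from the protocol article)

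| Input | Value | Section |
|---|---|---|
| Required number before loss | 300 | Statistical analysis |
| Loss to follow-up | 5% | Statistical analysis |
| Number to randomise | 2 × 158 = 316 | Statistical analysis |
| Number to randomise | 300 | Abstract (Methods); Patients |
| TIPP arm, as half of the population | 150, implying 300 | Surgical Techniques |
| Chronic pain, Lichtenstein against TIPP | 25% against 10% | Statistical analysis |
| α and power | 0.05 and 80% | Statistical analysis |

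The article does not say whether α is one- or two-sided. Two-sided is assumed for the power figures below.

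**Step 1: reproduce the plan's 2 × 158.** Number to randomise = required number / (1 − loss).

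- In total: 300 / 0.95 = 315.8, rounded up to 316.
- Per arm: 150 / 0.95 = 157.9, rounded up to 158, and 2 × 158 = 316.

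The figure reproduces, so 316 is a correctly worked inflation of 300 and not a slip.

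**Step 2: evaluable patients under each total.** Evaluable = randomised × (1 − loss).

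- 316 randomised: 316 × 0.95 = 300.2, which meets the stated 300.
- 300 randomised: 300 × 0.95 = 285, or about 142 per arm, which is 300 − 285 = 15 short.

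**Step 3: what the shortfall costs in power.** For 25% against 10%, the exact power of the uncorrected two-sided chi-square test is:

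- 150 per arm: 93.8%
- 142 per arm: 92.6%

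The drop is 1.2 percentage points. The normal approximation can be followed by hand. With n per arm and mean proportion (0.25 + 0.10)/2 = 0.175,

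power = Φ{[0.15 × √n − 1.96 × √(2 × 0.175 × 0.825)] / √(0.25 × 0.75 + 0.10 × 0.90)}

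- n = 150: (1.837 − 1.053) / 0.527 = 1.488, so power is 93.2%.
- n = 142: (1.787 − 1.053) / 0.527 = 1.394, so power is 91.8%.

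Both methods show the same small loss, and both leave power well above 80%.

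**Step 4: why power stays so high.** Solving the same approximation for 80% power gives 100 per arm (200 in total), or 113 per arm (226 in total) with a continuity correction. One-sided, the totals are 158 and 184. None of these is 300, so the base figure does not follow from the inputs stated beside it. That is a separate matter from the present one, but it explains why 285 evaluable patients would still give ample power on the stated rates.

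**The case against.** The strongest case against is that little follows from the discrepancy. With 285 evaluable patients the trial exceeds the larger of the two two-sided requirements in the working by 285 − 226 = 59 patients, and power stays near 92% against a target of 80%. No inferential aim of the trial is at risk. This stands, and it limits the weight of the point.

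Three further arguments are fair in part.

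- Surgical Techniques gives 300 only by implication, in a description of operations and not as a recruitment target. That is correct; the direct conflict lies between Statistical analysis on one side and the Abstract and Patients section on the other.
- The practical harm is inferred. Allocation runs through a telephone call to one trial centre, which pulls the envelope, so a hospital would not close recruitment on its own reading of the Patients section. The article gives neither the length of the list nor a rule for closing recruitment. That is also correct, but it moves the question to the trial centre, which needs a single number just as much.
- Statistical analysis is the only section that derives the number, so it could be taken as the controlling text, with 300 elsewhere carried over from before the inflation. This is the likely explanation, but the article does not say so.

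A last argument is that copying 316 into more sections would spread a figure whose base is not supported by the stated inputs. The base does need its own justification. Whatever base is settled, though, the trial still needs one randomisation total, stated the same way throughout.

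The discrepancy cannot be put down to the brevity of a journal article. Nothing has been left out: both totals are printed, and no fuller document could make both true.

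**Conclusion.** The concern holds. Two sections give 300 as the number randomised, a third implies it, and Statistical analysis gives 316; nothing in the article reconciles them. The arithmetic behind 316 is sound, so this is an inconsistency between sections and not a miscalculation.

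Its size is 16 randomised patients, or 15 evaluable patients at the plan's own 5% loss. In power it is 93.8% against 92.6% for 25% against 10%, assuming a two-sided chi-square test at 0.05, equal arms and loss shared evenly between them. It should not be read as saying that power would fall below 80%. It should be corrected because the randomisation target is a figure the trial relies on, and as written either total breaches part of the protocol.

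**What to change.** State one target throughout: 316 randomised (158 per arm) to obtain 300 evaluable (150 per arm), as Statistical analysis already plans. Correct the Abstract, the Patients section and Surgical Techniques to match, making clear wherever 300 is kept that it means evaluable patients. Confirm that the randomisation list and the envelope series run to at least 316.

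If the base of 300 is revised when its derivation is reviewed, apply the same division by 0.95 to the new base and carry the resulting single total into every section.

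The cost is wording in three places and a check of the list and envelope count. No patients are added beyond those Statistical analysis already provides for.

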### Randomisation

The randomisation list was generated by using the website randomisation.com . According to this list a random allocation of Lichtenstein and TIPP method was performed. Randomisation will take place by pulling a sealed envelope after phone call to the trial centre prior to incision at the theatre.

Operation forms are blinded in the electronic patients files and not available for the independent outpatient clinic researcher. The incision of the skin and anterior approach will be the same for both techniques.

## Conclusion

The TULIP is a double blind randomised controlled trial that aims to show a reduction in direct postoperative- and chronic pain after anterior inguinal hernia repair with placement of a soft mesh either in the inguinal canal (Lichtenstein) or in the preperitoneal space (TIPP).

Hypothetically the TIPP technique reduces chronic pain drastically compared to Lichtenstein because of the placement of the soft mesh in the preperitoneal space.
